### Trial setting

2.3.

We will conduct the Ultra-ECMO trial in the Department of Emergency Medicine at the First Affiliated Hospital of Nanjing Medical University, which is capable of initiating ECMO therapy for nearly 100 critically ill patients annually.

### Inclusion and exclusion criteria

2.4.

Patients ≥18 years of age receiving VA-ECMO therapy, such as extracorporeal cardiopulmonary resuscitation, will be eligible for inclusion in the Ultra-ECMO trial. Additional key inclusion criteria include (1) IMV onset of >72 h, (2) no pregnancy, (3) ECMO duration of >72 h, (4) RCS or CA with a cardiac origin, (5) no enrollment in another clinical trial, (6) a consent form signed by the guardian has been provided, and (7) a description of CPE on high-resolution chest computed tomography images has been given by two radiologists with ≥5 years of diagnostic experience who are unaware of the clinical diagnosis.

Meanwhile, the exclusion criteria for patient enrollment are as follows: (1) trauma; (2) written informed consent has not been provided by close relatives; (3) the patient has contraindications for fiberoptic bronchoscopy examination; (4) lung ultrasound images are blurry; (5) pneumothorax or massive pleural effusion; (6) ECMO is being used as a bridge for heart transplantation; and (7) the patient developed adverse events that complicate weaning from IMV (e.g., intracranial hemorrhage, thromboembolism, severe infection).

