**Methods:**

The Ultra-ECMO trial is a randomized controlled, open-label, single-center prospective superiority trial. At the onset of ECMO initiation, we will divide patients randomly into an intervention group and a control group in a 1:1 ratio. The control group will adopt protective ventilation settings [initial tidal volume: 6 ml/kg of predicted body weight (PBW)] for ventilation, and the intervention group will adopt ultra-protective ventilation settings (initial tidal volume: 4 ml/kg of PBW) for ventilation. The procedure is expected to last 72 h, after which the ventilator settings will be at the intensivists' discretion. The primary outcome is the VFD number at 28 days after inclusion. The secondary outcomes will include respiratory mechanics; analgesic/sedation dosage; lung ultrasound score; interleukin-6, interleukin-8, and monocyte chemotactic protein-1 levels in broncho-alveolar lavage fluid at the moment of enrollment (T0), 24, 48, and 72 h (T1, T2, and T3, respectively) after ECMO initiation; total time (in days) required for ECMO weaning; length of stay in the intensive care unit; total cost of hospitalization; amounts of resuscitative fluids; and in-hospital mortality.

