### Recruitment, randomization, and blinding

2.5.

The Ultra-ECMO trial will include patients who meet the abovementioned eligibility criteria. Formal information about the trial and an official copy of the informed consent form will be sent to their guardians. We will assign participants to an intervention arm or a control arm in a random manner, with those in the former group receiving ultra-protective VT and those in the latter receiving 72 h of protective VT. Guardians will also be informed that they are allowed to drop out of the trial at any time.

The randomization list will be computer-generated according to a simple randomization principle using a ratio of 1:1 by the Clinical Research Board of the School of Public Health of Nanjing Medical University. Participants will be assigned to each group by an independent trial assistant after verification of patient eligibility. Once group allocation has been completed, local investigators will register the record, then reveal the group allocation to care providers, who will deliver the intervention.

Trial assistants responsible for group allocation will be blinded to both groups of patients, but blinding of care providers is impracticable as ventilatory settings and respiratory mechanics measurements are part of routine daily clinical practice. The outcome assessors, data analysts and statisticians will not know the group allocation.

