### Interventions

2.6.

At the onset of ECMO initiation, all participants will be screened by therapists. Once the patient meets the inclusion criteria and is finally enrolled, the therapists will provide the selected intervention. We will assign patients in the intervention group to receive ultra-protective VT after randomization (initial settings: VT, 4 ml/kg of PBW; PEEP, 10 cmH_2_O; respiratory rate, 10 min^−1^; Vt may be decreased stepwise by 0.5 ml/kg PBW if the plateau pressure is >30 cmH_2_O) (17).

Patients in the control group will be managed using a protective VT strategy after randomization (initial settings: VT, 6 ml/kg of PBW; PEEP, 10 cmH_2_O; respiratory rate, 10 min^−1^; Vt may be decreased stepwise by 0.5 ml/kg of PBW if the plateau pressure is >30 cmH_2_O).

We will set the sweeping gas flow of ECMO, targeting a PaCO_2_ range of 35–45 mmHg, and the FiO_2_ value of the ventilator may be increased if PaO_2_ in the right upper limb decreases to <60 mmHg during the course of Vt and PEEP adjustments.

Furthermore, a hybrid veno-arterio-venous ECMO mode will be considered if differential oxygenation happens (18). Differential oxygenation refers to the lower body being perfused by ECMO-oxygenated blood while the upper body (coronaries, right arm, brain) receives hypoxemic blood pumped by the native heart. This pathophysiological phenomenon often results from the recovery of native left ventricular function and simultaneous severe lung failure. If optimized ventilation fails to solve this issue, it will be necessary to employ veno-arterio-venous ECMO in consideration of the potential for hypoxic damage to the brain and heart (19, 20).

At the moment of enrollment (T0), investigators will take charge of assessing and collecting pre-defined respiratory mechanics parameters; IL-6, IL-8, and MCP-1 levels; LUS; and other trial data as baseline information. The same procedure will be performed repeatedly at 24, 48, and 72 h (T1, T2, and T3, respectively) after ECMO initiation (Figure 2). After 72 h, the mechanical ventilation strategy in both groups will be changed at the intensivists' discretion.

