### Data collection and management

2.7.

The total duration of ECMO treatment, total time (in days) on IMV, ICU length of stay, analgesic/sedation dosage, all-cause hospital mortality, levels of inflammatory factors in BALF, LUS, amounts of fluid infusion, and total hospitalization cost will be calculated using patient medical records (Table 6).

**Table 6 T6:** Scheduled events and timeline for the ultra-ECMO trial.

		Study period					
Timepoint		Eligibility/Allocation	Post-Allocation			Close-out	
		T0 ECMO initiation	T1 24 h after ECMO	T2 48 h after ECMO	T3 72 h after ECMO	T4 28 days after ECMO	Tx ICU discharge day
Enrollment	Eligibility check	×					
	Informal consent	×					
	Allocation	×					
Intervention	Ultra-protective or protective VT group	×					
Assessments	Demorgraphic data	×					
	Comorbidity	×					
	Clinical characteristics	×					
	Respiratory mechanics parameters	×	×	×	×		
	LUS	×	×	×	×		
	Levels of inflammatory factors in BALF	×	×	×	×		
	In-hospital mortality		×	×	×	×	×
	RASS score	↔					
	VIS	↔					
	Amounts of resuscitative fluids		×	×	×	×	×
	Sedation and NMBA dose	↔					
	ICU LOS	↔					
	Total length of ECMO weaning	↔					
	Total lenght of IMV weaning	↔					
	Total cost for hospitalization						×
	Total hospital LOS	↔					
	28-day VFD	↔					

VT, tidal volume; VFD, ventilator-free day; ICU, intensive care unit; LOS, length of stay, VIS, vasoactive inotrope score; RASS, richmond agitation sedation scal; LUS, lung ultrasound score; BALF, broncho-alveolar lavage fluid.

We will not consider missing values for primary and secondary outcomes during hospitalization. However, missing values could appear specific to patients who survive to hospital discharge. If so, we will contact patients or their next of kin at day 28 to assess the pre-defined outcomes.

Clinical data will include but are not limited to general characteristics (age, sex, weight, height), comorbidities, original disease, the Acute Physiology and Chronic Health Evaluation II score, partial pressure of arterial oxygen/inspired oxygen fraction, PEEP, VT (in ml/kg of PBW), respiratory rate (in breaths/min), DP, P_plat_, P_es_, P_tp_, P_mean_ (in cm of water), C_stat_ (in ml/cmH_2_O), R (in cmH_2_O/L/s), arterial blood PaO_2_ and PaCO_2_ values (in mmHg), and mechanical power (in J/min).

We will also monitor the clinical conditions as well as the ECMO running status and collect any records.

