#### Primary outcome analysis

2.9.2.

The primary outcome is the 28-day VFD number, which will be determined by the intention-to-treat analysis (ITT) (21), regardless of whether the allocated ventilation strategy was effectively applied or not. The primary outcome will be reported in each group in the form of means with standard deviation values or medians with interquartile ranges. Student's *t* test or the Mann–Whitney *U* test will support related comparisons of the 2 groups while considering their distribution characteristics.

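### The ECMO-duration inclusion criterion is written as achieved time beyond 72 h, so it cannot be verified at ECMO initiation, when patients are screened and randomised

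*Protocol article*

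**What the plan says.** Section 2.4 (Inclusion and exclusion criteria) reads: "Additional key inclusion criteria include (1) IMV onset of >72 h, (2) no pregnancy, (3) ECMO duration of >72 h". Neither duration is qualified by a word such as expected or anticipated.

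The timing of enrolment is given in several places:

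- Abstract, Methods: "At the onset of ECMO initiation, we will divide patients randomly into an intervention group and a control group in a 1:1 ratio".
- Section 2.6 (Interventions): "At the onset of ECMO initiation, all participants will be screened by therapists".
- Section 2.5 (Recruitment, randomization, and blinding): "Participants will be assigned to each group by an independent trial assistant after verification of patient eligibility".
- Table 6 (section 2.7) marks the eligibility check, consent and allocation in one column only, headed "T0 ECMO initiation".

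The intervention has the same length as the criterion. The Abstract says: "The procedure is expected to last 72 h, after which the ventilator settings will be at the intensivists' discretion". Follow-up measurements are counted from the start of ECMO: "The same procedure will be performed repeatedly at 24, 48, and 72 h (T1, T2, and T3, respectively) after ECMO initiation" (section 2.6).

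Section 2.9.2 commits the primary outcome to intention to treat, "regardless of whether the allocated ventilation strategy was effectively applied or not".

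**The concern.** A criterion that must be checked before allocation has to rest on facts available before allocation. Time on ECMO beyond 72 h is not available at ECMO initiation. Someone running the trial must then either apply the criterion later or move randomisation later, and the article supports neither.

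Applying it later is the option that threatens the comparison. Patients who die, are decannulated or (on one reading of criterion (1)) come off the ventilator within 72 h would fail an inclusion criterion because of what happened under the assigned ventilation. Care providers know the allocation (section 2.5). The Introduction hypothesises that the ultra-protective strategy eases weaning and may even reduce in-hospital mortality. Early weaning and early death also bear directly on ventilator-free days. Restricting the analysis to patients still on support at 72 h would thus select on events that the treatment is hypothesised to change, and the arms would no longer be comparable by randomisation.

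**Working it through.** **1. Criterion (3) against the schedule.** At T0 (ECMO initiation) elapsed ECMO time is 0 h, so a requirement of more than 72 h cannot be verified. There are three ways to read it.

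| Reading | Consequence | Fits the article? |
|---|---|---|
| Already met at enrolment | T0 falls more than 72 h after ECMO initiation. T1, T2 and T3 (24, 48 and 72 h after ECMO initiation) have passed before T0, and the intervention is no longer early | No: contradicts the Abstract, sections 2.1 and 2.6, and Table 6 |
| Met later, checked at 72 h | Eligibility is settled only as the 72 h intervention ends, after allocation | No: contradicts section 2.5, which puts verification before assignment |
| Expected duration, judged at T0 | Can be checked before allocation | Yes, but the text does not say it |

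**2. Criterion (1).** Onset of ventilation more than 72 h earlier can be known at T0, but it selects patients already ventilated for three days, which sits badly with an early strategy. If ventilation lasting more than 72 h is meant, the fault is the same as in criterion (3).

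**3. Does the analysis text settle it?** Section 2.9.2 deals with whether the strategy was applied. The end of section 2.6 keeps patients with intervention-related adverse events in their group. Neither says what happens to a randomised patient who dies or leaves ECMO before 72 h.

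**4. The planned sample size, reproduced.** Inputs from section 2.8: means 7.1 and 9.2 (difference 2.1), SDs 8.8 and 9.3, two-sided α 0.05, power 80%.

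- Pooled SD = √[(8.8² + 9.3²)/2] = √81.965 = 9.053.
- n per group = 2 × 81.965 × (1.960 + 0.842)² / 2.1² ≈ 292, with power 80.0%. The t-test version gives 292.7, with power 79.9% at 292.
- Total = 584 × 1.05 = 613.2, rounded up to 614, or 307 per arm.

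The stated figures reproduce. The fault is in the eligibility wording, not in the arithmetic.

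**5. Power if patients were removed (illustration).** The article gives no share leaving support within 72 h, so the share x is assumed. Power = Φ(2.1 / [9.053 × √(2/n)] − 1.960), with n = 307 × (1 − x) and no other loss.

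| Assumed x | n per arm | Power |
|---|---|---|
| 5% | 292 | 80.0% |
| 20% | 246 | 72.9% |
| 40% | 184 | 60.5% |

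The difference and SDs are held fixed, although removing these patients would change both.

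**6. Direction of bias if patients were removed (illustration).** Every input here except the 7.1 is assumed.

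- *Early deaths removed.* Both arms have a true mean of 7.1 (50% survivors × 14.2 days, deaths scored 0), so the true difference is 0. With early deaths of 20% in control and 25% in intervention, the retained means are 7.1/0.80 = 8.88 and 7.1/0.75 = 9.47, an apparent gain of 0.59 days.
- *Early liberations removed.* In control, 80% are retained with mean 8. In intervention, 5% of patients come off support before 72 h with 25 days instead of staying on with 20. The true difference is 0.05 × 5 = +0.25 days. The retained intervention mean is (0.80 × 8 − 0.05 × 20)/0.75 = 7.20, an apparent difference of −0.80 days.

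The bias can run either way and can reverse the sign.

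**The case against.** The strongest reply is that one word is missing. If the authors meant ECMO expected to last more than 72 h, the criterion is assessable at T0 and agrees with the rest of the design. The other text leans towards retention: assignment follows verification of eligibility, the analysis is by intention to treat, and patients with intervention-related adverse events stay in their group. This stands as evidence of intent. It does not make the written criterion usable, and it leaves the status of early deaths and early weaners open.

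A reader might infer that the protocol breaks randomisation and intention to treat outright. The article does not support that. It nowhere says that patients failing the 72 h condition are removed, and if all randomised patients are analysed the randomised comparison stays intact.

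A reader might also infer that losses would far exceed the 5% dropout allowance, or that tidal volume is known to alter early death and weaning. The article gives no early-exit share, and the second statement is the trial's hypothesis, not an established fact.

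The bias examples are constructed. The first needs extra early deaths to be exactly offset by fewer later ones, removes deaths only, and scores deaths as 0, a rule the article does not state. They show that bias is possible, not how large it would be.

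**Conclusion.** The point holds for criterion (3). As written, it cannot be verified when the article says eligibility is verified, and both literal readings contradict the stated design. Criterion (1) is ambiguous and must be reconciled with an early strategy, but it is not necessarily a condition on the future.

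The harm to the intention-to-treat analysis is conditional on the criterion being applied after allocation, which the article neither states nor rules out. Its size cannot be derived from the article: power of about 80%, 73% or 60% corresponds to assumed removals of 5%, 20% or 40%, and the bias figures rest on assumed proportions throughout. The case for correction rests on the contradiction in the text, which determines who enters the primary analysis, and not on those figures.

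**What to change.** - Restate criteria (1) and (3) as conditions assessed and recorded before randomisation: on invasive ventilation and VA-ECMO at enrolment, with support judged at that moment as expected to exceed 72 h.
- State that every randomised patient stays in the primary analysis, including those who die or are weaned before 72 h.
- Confirm that the planning means and SDs in section 2.8 describe that whole randomised population.
- Use one time origin for T1 to T3 and for the 28-day window. The Abstract counts the 28 days from inclusion, while Table 6 counts them from ECMO. The two coincide only if enrolment does not lag behind ECMO initiation.

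The cost is a short amendment to two criteria and the time origin. The downside is that some patients with short support stay in and slightly dilute the contrast between strategies. The 292 per group is unchanged arithmetically.

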### Recruitment, randomization, and blinding

2.5.

The Ultra-ECMO trial will include patients who meet the abovementioned eligibility criteria. Formal information about the trial and an official copy of the informed consent form will be sent to their guardians. We will assign participants to an intervention arm or a control arm in a random manner, with those in the former group receiving ultra-protective VT and those in the latter receiving 72 h of protective VT. Guardians will also be informed that they are allowed to drop out of the trial at any time.

The randomization list will be computer-generated according to a simple randomization principle using a ratio of 1:1 by the Clinical Research Board of the School of Public Health of Nanjing Medical University. Participants will be assigned to each group by an independent trial assistant after verification of patient eligibility. Once group allocation has been completed, local investigators will register the record, then reveal the group allocation to care providers, who will deliver the intervention.

Trial assistants responsible for group allocation will be blinded to both groups of patients, but blinding of care providers is impracticable as ventilatory settings and respiratory mechanics measurements are part of routine daily clinical practice. The outcome assessors, data analysts and statisticians will not know the group allocation.

### Interventions

2.6.

At the onset of ECMO initiation, all participants will be screened by therapists. Once the patient meets the inclusion criteria and is finally enrolled, the therapists will provide the selected intervention. We will assign patients in the intervention group to receive ultra-protective VT after randomization (initial settings: VT, 4 ml/kg of PBW; PEEP, 10 cmH_2_O; respiratory rate, 10 min^−1^; Vt may be decreased stepwise by 0.5 ml/kg PBW if the plateau pressure is >30 cmH_2_O) (17).

Patients in the control group will be managed using a protective VT strategy after randomization (initial settings: VT, 6 ml/kg of PBW; PEEP, 10 cmH_2_O; respiratory rate, 10 min^−1^; Vt may be decreased stepwise by 0.5 ml/kg of PBW if the plateau pressure is >30 cmH_2_O).

We will set the sweeping gas flow of ECMO, targeting a PaCO_2_ range of 35–45 mmHg, and the FiO_2_ value of the ventilator may be increased if PaO_2_ in the right upper limb decreases to <60 mmHg during the course of Vt and PEEP adjustments.

Furthermore, a hybrid veno-arterio-venous ECMO mode will be considered if differential oxygenation happens (18). Differential oxygenation refers to the lower body being perfused by ECMO-oxygenated blood while the upper body (coronaries, right arm, brain) receives hypoxemic blood pumped by the native heart. This pathophysiological phenomenon often results from the recovery of native left ventricular function and simultaneous severe lung failure. If optimized ventilation fails to solve this issue, it will be necessary to employ veno-arterio-venous ECMO in consideration of the potential for hypoxic damage to the brain and heart (19, 20).

At the moment of enrollment (T0), investigators will take charge of assessing and collecting pre-defined respiratory mechanics parameters; IL-6, IL-8, and MCP-1 levels; LUS; and other trial data as baseline information. The same procedure will be performed repeatedly at 24, 48, and 72 h (T1, T2, and T3, respectively) after ECMO initiation (Figure 2). After 72 h, the mechanical ventilation strategy in both groups will be changed at the intensivists' discretion.

**Figure 2 F2:**
[figure not shown]
Flowchart of the study design. ECMO, extracorporeal membrane oxygenation; VT, tidal volume; PBW, predicted body weight; CA, cardiac arrest; PEEP, positive end-expiratory pressure; CPE, cardiogenic pulmonary edema; ICU, intensive Care Unit; LUS, lung ultrasound score; VFD, ventilator-free days.

Patients in both groups will receive deep sedation (i.e., targeting a Richmond Agitation Sedation Scale score of −3 or −4 points) during the intervention period. Although deep sedation will be adopted, it is still recommended to administer a neuromuscular blocking agent specific to the situation of patient–ventilator asynchrony.

In case adverse events occur due to the intervention, patients will be managed by the attending physicians at their discretion but still remain in the allocation group to support later data analysis.

### Data collection and management

2.7.

The total duration of ECMO treatment, total time (in days) on IMV, ICU length of stay, analgesic/sedation dosage, all-cause hospital mortality, levels of inflammatory factors in BALF, LUS, amounts of fluid infusion, and total hospitalization cost will be calculated using patient medical records (Table 6).

**Table 6 T6:** Scheduled events and timeline for the ultra-ECMO trial.

		Study period					
Timepoint		Eligibility/Allocation	Post-Allocation			Close-out	
		T0 ECMO initiation	T1 24 h after ECMO	T2 48 h after ECMO	T3 72 h after ECMO	T4 28 days after ECMO	Tx ICU discharge day
Enrollment	Eligibility check	×					
	Informal consent	×					
	Allocation	×					
Intervention	Ultra-protective or protective VT group	×					
Assessments	Demorgraphic data	×					
	Comorbidity	×					
	Clinical characteristics	×					
	Respiratory mechanics parameters	×	×	×	×		
	LUS	×	×	×	×		
	Levels of inflammatory factors in BALF	×	×	×	×		
	In-hospital mortality		×	×	×	×	×
	RASS score	↔					
	VIS	↔					
	Amounts of resuscitative fluids		×	×	×	×	×
	Sedation and NMBA dose	↔					
	ICU LOS	↔					
	Total length of ECMO weaning	↔					
	Total lenght of IMV weaning	↔					
	Total cost for hospitalization						×
	Total hospital LOS	↔					
	28-day VFD	↔					

VT, tidal volume; VFD, ventilator-free day; ICU, intensive care unit; LOS, length of stay, VIS, vasoactive inotrope score; RASS, richmond agitation sedation scal; LUS, lung ultrasound score; BALF, broncho-alveolar lavage fluid.

We will not consider missing values for primary and secondary outcomes during hospitalization. However, missing values could appear specific to patients who survive to hospital discharge. If so, we will contact patients or their next of kin at day 28 to assess the pre-defined outcomes.

Clinical data will include but are not limited to general characteristics (age, sex, weight, height), comorbidities, original disease, the Acute Physiology and Chronic Health Evaluation II score, partial pressure of arterial oxygen/inspired oxygen fraction, PEEP, VT (in ml/kg of PBW), respiratory rate (in breaths/min), DP, P_plat_, P_es_, P_tp_, P_mean_ (in cm of water), C_stat_ (in ml/cmH_2_O), R (in cmH_2_O/L/s), arterial blood PaO_2_ and PaCO_2_ values (in mmHg), and mechanical power (in J/min).

We will also monitor the clinical conditions as well as the ECMO running status and collect any records.

Delegated team members will take charge of inputting data in the electronic case report form, and experienced clinical research associates will take charge of the data monitoring. Team members will store research data under each participant's study identification code, which will include the first letter of the first and family names of the participant, together with their inclusion number. Only the research team will have the right to possess the key to the identification code list during the study. Detailed information regarding the identification of patients will not be available in any resulting publications.

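### The 28-day horizon and T0 each have two starting points (inclusion or enrolment, and ECMO initiation), and the article does not establish that these are the same moment

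*Protocol article*

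**What the plan says.** **28-day horizon.** The abstract (Methods) states: "The primary outcome is the VFD number at 28 days after inclusion". In Table 6 (section 2.7) the day-28 column is headed "T4 28 days after ECMO". Sections 2.1, 2.2 and 2.9.2 name the 28-day ventilator-free days (VFD) without an origin. So does the day-28 contact with discharged patients in section 2.7.

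**T0.** Section 2.6 has "At the moment of enrollment (T0), investigators will take charge of assessing", and the abstract agrees. Table 6 labels the same column "T0 ECMO initiation".

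**T1 to T3.** These have a single origin throughout. Section 2.6 puts them "at 24, 48, and 72 h (T1, T2, and T3, respectively) after ECMO initiation", and the abstract and Table 6 match. Section 2.6 starts the assigned tidal volume after randomisation.

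**When enrolment happens.** The abstract randomises, and section 2.6 screens, at the start of ECMO. Table 6 marks eligibility check, consent, allocation and intervention in the T0 column. Section 2.4, however, lists among the inclusion criteria an ECMO duration of >72 h, IMV onset of >72 h, signed guardian consent, and a CT description of cardiogenic pulmonary oedema that "has been given by two radiologists with ≥5 years of diagnostic experience". Section 2.5 allocates only once eligibility has been verified.

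**The concern.** VFD is a count inside a fixed window, so its value depends on when the window opens. If the window opens at ECMO initiation and randomisation comes later, ventilator days before randomisation count against the patient, and the window closes before 28 days of randomised follow-up. Two analysts, one following the abstract and one following Table 6, could then report different VFD values for the same patients. The article also does not say which clock the planning means of 7.1 and 9.2 belong to.

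The repeated measurements raise a related problem. If T1 to T3 are timed from ECMO but treatment starts at randomisation, the same visit label covers different amounts of assigned treatment in different patients. This affects the BALF cytokines, the lung ultrasound score and respiratory mechanics.

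**Working it through.** **1. The plan's own figure.** Section 2.8 gives means 7.1 and 9.2 (difference 2.1), SDs 8.8 and 9.3, two-sided α 0.05 and 80% power. By the normal approximation, n per group = (1.960 + 0.842)² × (8.8² + 9.3²) / 2.1² = 7.85 × 163.93 / 4.41 ≈ 292. This reproduces the stated 292. A noncentral t calculation gives 293, with power 0.799 at 292. The total of 614 is 584 × 1.05 = 613.2, rounded up. The sample size is not at fault here; the issue is the time origin.

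**2. The origins side by side.**

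| Item | Abstract | Section 2.6 | Table 6 |
|---|---|---|---|
| 28-day horizon | inclusion | not given | ECMO |
| T0 | enrolment | enrolment | ECMO initiation |
| T1–T3 | ECMO initiation | ECMO initiation | ECMO |
| Start of assigned tidal volume | not given | after randomisation | T0 column |

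Two items carry two origins: the 28-day horizon and T0.

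**3. The lag.** Let L be the days from ECMO initiation to inclusion.
- If enrolment is at ECMO initiation, L = 0 and the clocks agree.
- If CT reading and consent take time after ECMO starts, L > 0 and varies by patient. The article gives no durations.
- If the ECMO criterion in section 2.4 means time already elapsed, L > 3, because section 2.5 requires eligibility to be verified before allocation. T1 to T3 would then precede allocation, although Table 6 places them after it.

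The IMV criterion does not settle this, because a patient already ventilated for more than three days could meet it at ECMO initiation.

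**4. Effect on VFD.** Take a survivor ventilated throughout the lag and weaned t days after inclusion:
- inclusion clock: VFD = max(0, 28 − t)
- ECMO clock: VFD = max(0, 28 − L − t)

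The ECMO-clock ceiling is 28 − L, which is 25 at L = 3. The loss is L days if t ≤ 28 − L, and less for patients weaned in the last L days of the inclusion window. With p the share of an arm with VFD > 0, the arm mean therefore falls by at most about L × p.

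**5. Effect on the treatment difference.** Both arms fall, so the difference changes by about L × (p₁ − p₀). The documents do not give p₁ − p₀. For an assumed gap of 5 to 10 percentage points at L = 3:
- 3 × 0.05 = 0.15 day
- 3 × 0.10 = 0.30 day

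Against the planned 2.1 days this is 0.15/2.1 ≈ 7% to 0.30/2.1 ≈ 14%. At L = 0 it is zero.

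**6. Effect on T1 to T3.** Hours of assigned tidal volume at each visit are the nominal hour minus 24L. At L = 1, T1, T2 and T3 fall at 0, 24 and 48 h of assigned treatment. At L = 3, T3 falls at 0 h.

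**The case against.** The strongest reply is that the article treats inclusion and ECMO initiation as one event. The abstract, section 2.6 and Table 6 all place screening or allocation there, and on that schedule the clocks coincide. Section 2.4 does not say that the >72 h on ECMO must have elapsed before enrolment. Expected duration would fit a 72 h intervention starting with ECMO, whereas the elapsed reading makes the visit schedule impossible. This much stands: the eligibility rules do not prove that the clocks must differ. A reader might infer that they do, but that depends on one reading of the criterion. What does not stand is that the lag can be taken as zero, since an ECMO duration of >72 h cannot be observed at ECMO initiation and section 2.5 requires eligibility to be verified first.

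A second reply is that the only sentence giving the primary outcome an origin is the abstract's. The ECMO origin comes from a column head in Table 6, and the VFD row carries a continuous arrow rather than a mark at T4. This is fair and narrows the point, but the schedule still places day 28 on a different clock from the outcome.

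A third reply concerns size. If 40 to 60% of patients have VFD > 0 (an assumption), a three-day lag lowers mean VFD by up to 3 × 0.4 = 1.2 to 3 × 0.6 = 1.8 days, and a reader might set that against the planned 2.1. That comparison is not valid: the first is a shift in level common to both arms, the second a difference between arms. The lag arises before allocation, so one clock applied to both arms does not by itself bias the comparison.

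**Conclusion.** The point holds as an inconsistency in the current text on the time origin of the primary outcome and on the meaning of T0. A mismatch between the visit clock and the start of treatment follows if there is any lag. T1 to T3 are not themselves inconsistent.

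The consequence depends on L, which the article does not give: none at L = 0, and a ceiling of 28 − L on the ECMO clock otherwise. At L = 3 the treatment difference changes by about 0.15 to 0.30 day under the assumed 5 to 10 point gap. The main harm is an endpoint window and an exposure time that are not pinned down, rather than a biased comparison. It should be corrected, and Table 2 says that enrolment has not begun.

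**What to change.** - State one day 0, the time of randomisation, for the 28-day VFD window and for T0 to T4. Align the abstract, section 2.6 and the column heads of Table 6.
- Record the interval from ECMO initiation to randomisation as a baseline variable.
- State in section 2.4 whether the >72 h criteria mean elapsed or expected time, and reconcile this with the abstract, section 2.6 and Table 6. Changing the clock alone would leave that conflict in place.

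The cost is protocol wording and case report form labels, with no extra patients or procedures. There is one small downside: if lags are real, BALF, ultrasound and mechanics sampling moves from the ECMO clock to the randomisation clock, so actual sampling times change.
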